##### Stroke severity and motor function

The (NIHSS) questionnaire will be used to measure stroke severity and motor function of upper and lower limbs. Two items (out of 11 items) of this questionnaire will be related to motor function of limbs [30]. The data obtained from this questionnaire will cover the section of body structure related to ICF. This questionnaire will have 11 items, each of which with 5 options and scores from 0 to 4 (a score of 0 indicates normal performance and a score of 4 indicates a severe defect in performance). Due to the special type of scoring, scores will eventually be obtained between 0 and 42, which will be divided as follows:0: No stroke symptoms1–4: Mild stroke5–15: Medium stroke16–20: Moderate to severe stroke21–42: Severe stroke

The validity of this questionnaire was confirmed using clinical predictor validity and its reliability was approved with Cronbach's alpha of 0.95 in Hinkle's study [31]. It should be noted that, in the present study, the original version of this questionnaire will be used by a neurologist.

##### Activities of daily living

The Barthel Index (BI) questionnaire will be used to measure the activities of daily living (covering the activities section of ICF). This questionnaire includes 10 key activities of daily living including: feeding, bathing, grooming, dressing, bowels, bladder, toilet use, transfers (bed to chair and back), mobility (on level surfaces) and stairs. In each item, scores are: 0 (dependent), 5 (need for major help), 10 (need for minor help) and 15 (independent). Finally, the ranking of people is done as follows:80–100: independent.60–79: slightly dependent.40–59: relatively dependent.20–39: very dependentLess than 20: completely dependent [32].

The validity and reliability of the Persian version of this tool were confirmed in a study conducted by Tagharrobi et al. [33] The validity of the questionnaire was confirmed using concurrent validity, comparison of known groups and exploratory factor analysis and the reliability was confirmed using Cronbach's alpha. The Cronbach's alpha coefficient of this instrument was reported as 0.99.

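### The printed Barthel item rule allows totals up to 150, but the ranking bands stop at 100

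*Protocol article*

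**What the plan says.** The Activities of daily living section sets out the instrument in three steps.

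- **Items:** "This questionnaire includes 10 key activities of daily living including: feeding, bathing, grooming, dressing, bowels, bladder, toilet use", followed by transfers, mobility and stairs. That makes ten.
- **Scores:** "In each item, scores are: 0 (dependent), 5 (need for major help), 10 (need for minor help) and 15 (independent"). No item is exempted, and no item-specific maximum is given.
- **Ranking:** "the ranking of people is done as follows:80–100: independent", then "60–79: slightly dependent", "40–59: relatively dependent", a band for 20–39 and a last band below 20.

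The section states no total range, no rescaling and no band above 100. It cites a source for the bands and a validation study of the Persian version. The Data collection section says that the attending neurologist completes the Barthel Index. The Data analysis section compares activities-of-daily-living scores between groups with an independent t-test.

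**The concern.** The item rule and the bands stand in the same paragraph and do not fit each other. A scale whose ten items all run to 15 cannot have 100 as its highest total.

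Two things depend on which statement the trial follows. The first is the ranking. Under the printed rule the best-functioning patients cannot be classified, and some patients who by the section's own labels need help with every activity are called independent. The second is the score itself. The Barthel Index is the trial's only measure of activities of daily living and carries the activities part of the ICF framework. If the printed rule were used, the between-group comparison would be made on a non-standard total. The cited validity and reliability would not carry over to it, and its means could not be read on a 0–100 scale.

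**Working it through.** **Inputs**, all from the Activities of daily living section: 10 items; permitted scores 0, 5, 10 and 15 in each; bands below 20, 20–39, 40–59, 60–79 and 80–100. One assumption: the total is the sum of the items. The section does not say so, but it is the plain reading of a score ranked on such bands.

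**Range.** Minimum 10 × 0 = 0; maximum 10 × 15 = 150. The plan's own upper limit of 100 is not reproduced.

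**Totals without a band.** Totals move in steps of 5, so there are 150/5 + 1 = 31 possible values. Those from 105 to 150, (150 − 105)/5 + 1 = 10 of them, fall in no band.

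**Same level on all ten items:**

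| Level on every item | Total | Printed band |
|---|---|---|
| Dependent | 10 × 0 = 0 | completely dependent |
| Major help | 10 × 5 = 50 | relatively dependent |
| Minor help | 10 × 10 = 100 | independent |
| Independent | 10 × 15 = 150 | none |

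**Help needed on every item, part minor and part major.** With k items at minor help and 10 − k at major help, the total is 10k + 5(10 − k) = 50 + 5k. The independent band starts at 80, so it is reached when 50 + 5k ≥ 80, that is k ≥ 6.

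- k = 5: 75, slightly dependent
- k = 6: 80, independent
- k = 10: 100, independent

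**Where the bands run out.** With i items independent and the rest at minor help, the total is 15i + 10(10 − i) = 100 + 5i. A single independent item (i = 1) gives 105, already outside every band.

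**What the bands require.** For 100 to be the highest possible total, the ten item maxima must sum to 100, an average of 10 per item, so 15 cannot be the maximum of every item. If even one item reaches 15, the other nine maxima must sum to 85, an average of 9.4. The maxima would then differ between items, and the printed rule would change the relative weights of the activities as well as the units. The article gives no item-specific maxima, so the correct values cannot be derived from it.

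**The case against.** The strongest reply is that this is a slip in condensing a known instrument. The section names an established index, cites a source for the bands and a validated Persian version, and has a neurologist complete it. The bands themselves point to an intended 0–100 total. On that reading the four values are those that occur somewhere on the form, and the trial data are unaffected. Nothing in the article says that a form will be built from this sentence. This stands as a limit on the consequences. It does not rescue the sentence, which says each item, labels 15 as independent without exception and carries no caveat.

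Three stronger readings are tempting but not supported.

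- A reader might infer that anyone needing help with every activity is ranked independent. Major help on all ten gives 50, which is relatively dependent. Among patients at minor or major help throughout, the label is wrong only from six minor-help items upwards.
- A reader might infer that the bands distort the trial's tests. The Data analysis section tests scores, and no planned test uses the Barthel categories. The sample size in Study design and setting rests on the NIHSS. A wrong item rule would apply to both arms alike and would not by itself favour either.
- A reader might see the same error in the Stroke severity and motor function section, where 11 items are described as "each of which with 5 options and scores from 0 to 4" (11 × 4 = 44) but "scores will eventually be obtained between 0 and 42". That section attributes the lower total to a special type of scoring and says that the original version will be used, so the gap is explained there.

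Nor can one say how many patients would be affected. That depends on how patients are distributed over the items, which the article does not give.

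**Conclusion.** The sentence is wrong as written: the printed rule tops out at 150, against bands that end at 100. This is an incorrect scoring rule for a named outcome, not detail left to a fuller document. If it were applied, ten of 31 possible totals would have no band, full independence among them, and patients at minor help on six or more items and major help on the rest would be ranked independent. The analysed score would not be on the scale that the bands imply.

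The result rests on summing the items and on taking the sentence at its word. The practical harm is conditional: it reaches the data only if the form follows the printed rule, and is confined to the article if the cited validated form is used. With no eligibility rule, sample-size input or planned test resting on the bands, a moderate rating is right.

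**What to change.** Replace the sentence that gives one set of scores for every item with the item-specific scores of the cited validated version. Confirm that the item maxima sum to 100, and state the total range as 0–100. Check that the form used by the neurologist offers only those options for each item, and add a 0–100 range check to it before any scoring. If the validated form is already in use, say so in the correction, so that readers know the data are unaffected.

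The cost is one corrected sentence and one form check. No patients, visits, instruments or analyses change.

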##### Quality of life

To assess the quality of life and the level of social participation (covering the social participation section of the ICF), the EQ-5D-3L (EuroQol group-5 Dimentions-3 Level) questionnaire including 5 questions on a 3-point Likert scale will be used. The final score of the questionnaire will be between 0 and 10. The validity and reliability of the Persian version were confirmed in a study done by Dastourani et al. [34] The construct validity and the differential validity were confirmed by testing the predetermined hypotheses and by the method of known groups, respectively. Cronbach's alpha coefficient of this questionnaire was reported as 0.89.

##### Depression

To assess the depression (covering the body structure section of ICF), the BDI-II (Beck Depression Inventory-II) questionnaire will be used, which includes 21 groups of sentences with a value scale of 0 to 3 expressing the patient’s feelings during the previous 2 weeks. The scores of this questionnaire are between 0 and 63. The validity and reliability of the Persian version of this questionnaire were confirmed in a study done by Hamidi et al. [35] The validity of the questionnaire was confirmed using descriptive and confirmatory factor analysis as well as convergent validity and its Cronbach's alpha was 0.93.

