### Implementation and evaluation of application in the live environment (clinical trial)

#### Study design and setting

At this stage, an interventional study will be conducted through patient blinding by an assessor physician and analyst to evaluate the effects of the application on patient self-care. The designed application will be installed on patients’ smartphones and the necessary training to use it will be given to the patients and their caregivers. This application will support Android 5 and above. The study population will include patients referring to one of the general hospitals in Kashan where sampling can be done in a convenient way. Patients with hemiplegia or hemiparesis caused by a recent stroke will be chosen for this purpose. Either the patient or his/her patient caregiver must have an Android-based smartphone and be able to work with it. At least 72 h must have passed since the stroke (The acute phase of the disease must have passed) and patients must have adequate consciousness and hearing and be willing to participate in the study. Exclusion criteria will include:Patients who have some levels of consciousness disorderPatients with cognitive disorders such as dementia or memory impairmentPatients with global aphasia

The formula “n = [(Z_1−α/2_ + Z_1−β_)^2^ * (σ_1_^2^ + σ_2_^2^)]/($$\overline{x }$$_1 _− $$\overline{x }$$_2_)^2^” with the reliability of 95% and the test power of 90% based on the mean and standard deviation of baseline NIHSS obtained in the same study [29] (Z_1−α/2_ = 1.96, Z_1−β_ = 1.282, σ_1_, σ_2_ = 8, $$\overline{x }$$_1_ = 5, $$\overline{x }$$_2_ = 12) was calculated as 27 patients, which increased to 30 patients according to the available facilities which, with a 10% sample dropout, will increase to 33 individuals. Accordingly, two groups each including 33 patients (intervention and control) with stroke (66 patients in total) who meet the inclusion criteria will be selected.

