#### Data collection

The required data will be collected using valid and reliable questionnaires that are introduced as follows. Data will be collected in three stages: prior to intervention (before the intervention and at the time of discharge), two months after the intervention and three months after the intervention (in the doctor's office or in the hospital outpatient clinic). Data from National Institute of Health Stroke Scale (NIHSS) and Barthel Index (BI) questionnaires and stroke complication checklist will be filled out by the attending neurologist and other questionnaires will be filled out by patients as self-report. Completion of questionnaires by patients will be done electronically and sent online through the application. Therefore, this survey will be considered as a “closed survey” since only registered users with a valid account can access the questionnaires and submit them. Application features will be inactive until patients, complete questionnaire items. After completion, application features will be activated and the questionnaire will be deactivated to prevent response duplications. The questionnaires will be reactivated two months and three months later. In order to ensure that no data will be missing, all fields and questions will be defined as mandatory in electronic questionnaires and patients will be warned to answer all questions before sending the questionnaire.

All online questionnaires will exactly be designed the same as paper questionnaires in terms of appearance, content and sequence of questions. That is, all the questions will be placed consecutively and not on separate pages. Therefore, it can be said that the validity and reliability reported for the paper version of questionnaire will also apply to the electronic version.

It is expected that the use of this application can improve the measured variables in the intervention group compared to the control group. Specifically, the research hypotheses are that patients in the intervention group have significant differences with those in the control group in terms of indicators of physical activity, depression, quality of life, medication adherence, satisfaction with treatment, and the number of complications.

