#### Data analysis

Data analysis will be performed using IBM SPSS 22 [43]. The data will be entered anonymously using codes and numbers, which can be decoded only by one of the researchers (except the assessor or the analyst). The data will be stored in this software application and supported by a backup on another system kept in another place. The data will be first presented in the form of descriptive statistics and frequency distribution tables. The normality of the data will be checked using the Kolmogorov–Smirnov test. Depending on the type of data distribution, the mean or median of the data will be used as a criterion. In case of normal distribution of data, the mean will be used and in case of abnormal distribution (non-parametric), the median will be used for statistical calculations. In order to determine the relationship between the scores of patients’ activities of daily living, quality of life, depression, medication adherence and patient satisfaction with patients’ group type (control or intervention), an independent t-test will be used. If there is a significant difference between the intervention group and the control group, the effect of the intervention will be specified. Repeated measures analysis of variance (ANOVA) will also be used to analyze multivariate and control the effects of confounding variables on dependent variables. Confounding variables will include: patient age, sex and educational level, which can affect the final results. In all tests, a significance level of 0.05 will be considered. Pearson or Spearman correlation coefficient (according to the type of variable distribution) will be used to determine the relationship between the usage duration of the program and the score of the measured variables. After categorizing the time of application usage, one-way ANOVA or Kruskal–Wallis’s test (depending on the type of variable distribution) will be used to determine the relationship between the measured variables and the time of application usage. Chi-square test will be used to determine the relationship between the type of complications in both groups. Also, to determine the relationship between the scores of the measured variables before and after the intervention, a paired t-test will be used in each group separately. Hypothesis H0 will indicate the absence of correlation and Hypothesis H1 will indicate the existence of correlation between the measured variables.

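### The baseline BDI-II can reach back before the stroke, so within-arm change from baseline should not be read as change in post-stroke depression

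*Protocol article*

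**What the plan says.** All of this is in the protocol article.

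- **Depression:** the BDI-II items express the patient's "feelings during the previous 2 weeks". No modified recall instruction is described.
- **Study design and setting:** the population is recent stroke ("Patients with hemiplegia or hemiparesis caused by a recent stroke will be chosen for this purpose"), and the entry rule is "At least 72 h must have passed since the stroke". No 14-day minimum is stated.
- **Data collection:** the first assessment is "prior to intervention (before the intervention and at the time of discharge". "Application features will be inactive until patients, complete questionnaire items", so the baseline BDI-II comes before any use of the app content. For follow-up, "The questionnaires will be reactivated two months and three months later".
- **Data analysis:** depression is among the scores compared between arms by an independent t-test, and a repeated measures ANOVA is also planned. A further analysis has the stated purpose "to determine the relationship between the scores of the measured variables before and after the intervention". The method named for this purpose is a within-arm one: "a paired t-test will be used in each group separately".

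**The concern.** A paired before-after test has a clear meaning only if both scores describe the same kind of period. Here the follow-up scores describe life after the stroke. The baseline score may describe, in part, life before it, and that part shrinks as the hospital stay lengthens. An apparent rise or fall in the BDI-II within an arm could then reflect the arrival of the stroke in the recall window, and its size would depend on length of stay.

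This goes beyond the usual weakness of uncontrolled before-after tests. That weakness concerns the cause of a change. Here, even as description, the change may not be a change in post-stroke depression. Depression is one of the conditions the app is meant to prevent and reduce (Intervention section), so a reader would naturally look at this result.

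**Working it through.** The article gives no figure for the BDI-II to reproduce. Its sample size rests on the NIHSS and is not affected.

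**Inputs.** Recall window 14 days (Depression). Earliest entry day 3, from the 72 h rule (Study design and setting). Baseline at discharge, follow-up at two and three months (Data collection). The day of discharge, *d*, is not given and is varied as an assumption.

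**Step 1: overlap at baseline.** Share of the window before the stroke: *f* = max(0, 14 − *d*)/14.

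| Discharge day *d* | Pre-stroke days | *f* |
|---|---|---|
| 3 | 11 of 14 | 79% |
| 5 | 9 of 14 | 64% |
| 7 | 7 of 14 | 50% |
| 10 | 4 of 14 | 29% |
| 14 or later | 0 of 14 | 0% |

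**Step 2: overlap at follow-up.** Taking two months as about 60 days after baseline, the window opens at about 60 − 14 = 46 days after baseline. It lies wholly after the stroke, and so does the month-3 window.

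**Step 3: effect on each comparison.** Suppose, for illustration, that the score averages the 14 days equally. Let mean mood be *P* before the stroke and *S* after it, and let *e* be the app effect.

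- Baseline mean: *fP* + (1 − *f*)*S*. Follow-up mean: *S* + *e* in the app arm, *S* in the control arm.
- Within-arm change: *f*(*S* − *P*) + *e* in the app arm, *f*(*S* − *P*) in the control arm.
- Between-arm difference, in follow-up score or in change: *e*. The overlap cancels.

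With assumed means *P* = 8 and *S* = 16:

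- *d* = 3: the false component is 0.786 × 8 = 6.3 points. With *e* = −5, the app arm changes by 6.3 − 5 = +1.3, the wrong direction.
- *d* = 7: the false component is 0.5 × 8 = 4.0. With *e* = −5, the change is −1.0.
- *d* = 14: the false component is 0, and the change equals *e*.

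**Step 4: simulation under the same assumed means.** There were 4,000 runs per row and 30 patients per arm. Assumed SDs were 6 for pre-stroke mood, 5 for the individual shift at stroke, 3 for baseline error and 5 for follow-up error.

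| *d* | *e* | Mean change, app arm | Paired test rejects | Between-arm test, follow-up score, rejects | Between-arm test, change, rejects |
|---|---|---|---|---|---|
| 3 | 0 | +6.3 | over 99% | 5.0% | 4.5% |
| 3 | −5 | +1.3 | 16% | 53% | 77% |
| 7 | 0 | +4.0 | 91% | 4.8% | 5.0% |
| 7 | −5 | −1.0 | 13% | 52% | 85% |
| 14 | 0 | 0.0 | 5.1% | 4.5% | 4.8% |
| 14 | −5 | −5.0 | over 99% | 53% | 91% |

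The between-arm tests hold their 5% level throughout, and the mean difference in change is −5.0 whenever *e* = −5. What the overlap costs there is precision: power for the difference in change is 77% at *d* = 3 against 91% at *d* = 14. The paired test loses its meaning at *d* = 3 and *d* = 7.

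**The case against.** The case against is substantial.

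- **The plan's inference is already between arms.** The hypotheses in Data collection compare the two groups, and Data analysis ties the intervention effect to a significant difference between them. The article nowhere says that an app effect will be read from the paired test. This stands. A reader might infer that the trial cannot show an app effect on depression. The documents do not support that: randomisation gives both arms the same baseline problem, and it cancels.
- **The overlap is conditional.** The 72 h rule is a minimum for entry, not the day of discharge, and 79% needs discharge at the first eligible moment. A reader might infer that much of the baseline score is pre-stroke mood. That is not established, because length of stay is not given and a share of days is not a share of score. Patients may weight recent days more heavily.
- **The direction is assumed.** An effective app looks harmful only if mood worsens with stroke by enough to outweigh the benefit. The article gives no BDI-II values, so the 8 and 16 above are illustrative. With *S* = *P* there is no distortion.
- **Within-arm tests cannot isolate an app effect for any outcome.** True, and a general comment on them would cover much of this. The mismatch of reference periods is specific to this outcome, however, and also touches the time effect in the ANOVA.

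A related remark on patient satisfaction, that the treatment being rated may differ between discharge and follow-up, is plausible. But the article states no recall period for that scale, so it is at most a secondary remark.

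**Conclusion.** The point holds in a limited form. For any patient discharged before day 14, the baseline BDI-II window includes pre-stroke days, by 79% of days at day 3 down to 0% from day 14. The within-arm paired test and the time effect from baseline in the repeated measures ANOVA may therefore compare different health states, and should not be reported as change in post-stroke depression. That mismatch needs only the stated recall window, the stated baseline timing and a discharge before day 14. The size and sign of any bias in points depend on assumptions that the article cannot settle.

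The randomised comparison at months 2 and 3 is valid, and no sample-size figure changes. It is a modest point, but worth acting on: the analysis that can mislead is written into the plan, and the correction is nearly free.

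**What to change.** 1. Remove the BDI-II from the within-arm paired t-tests.
2. If it stays in the repeated measures ANOVA, do not interpret its time effect from baseline.
3. Base the depression conclusion on the between-arm difference at months 2 and 3, by ANCOVA with the discharge BDI-II as covariate. The score is taken before the app content is unlocked, so it is a legitimate covariate whatever period it describes. In large samples ANCOVA is at least as precise as the unadjusted comparison of follow-up scores or the comparison of change.
4. Report days from stroke to baseline by arm, so that the overlap is known. The onset date is already needed to apply the 72 h rule.

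No visit, questionnaire or sample-size change is needed. The cost is analysis wording and the loss of a within-arm result that is hard to interpret.
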